## Abstract

**Background:**

Internationally, stroke and cardiac rehabilitation clinicians agree that current cardiac rehabilitation models are a suitable secondary prevention program for people following a transient ischaemic attack (TIA) or mild stroke. There is strong evidence for exercise-based cardiac rehabilitation in people with heart disease, however, the evidence for cardiac rehabilitation post-TIA or stroke is limited. Here we will explore the effectiveness and implementation of an integrated (TIA, mild stroke, heart disease) traditional exercise-based cardiovascular rehabilitation (CVR) program for people with TIA or mild stroke over 6-months.

**Methods:**

This type 1 effectiveness-implementation hybrid study will use a 2-arm single-centre assessor-blind randomised controlled trial design, recruiting 140 participants. Adults who have had a TIA or mild stroke in the last 12-months will be recruited by health professionals from hospital and primary healthcare services. Participants will be assessed and randomly allocated (1:1) to the 6-week CVR program or the usual care 6-month wait-list control group. Distance completed in the 6-min walk test will be the primary effectiveness outcome, with outcomes collected at baseline, 6-weeks (complete CVR) and 6-months in both groups. Other effectiveness outcome measures include unplanned cardiovascular disease-related emergency department and hospital admissions, daily minutes of accelerometer moderate-to-vigorous physical activity, body mass index, waist circumference, blood pressure, quality of life, anxiety and depression. Implementation outcomes will be assessed using the Reach, Effectiveness, Adoption, Implementation, Maintenance (RE-AIM) framework, including a cost-effectiveness analysis. Semi-structured interviews will be conducted with participants and CVR program health professionals, investigating the acceptability, value, and impact of the CVR program. Qualitative analyses will be guided by the Consolidated Framework for Implementation Research.

**Discussion:**

Few studies have assessed the effectiveness of cardiac rehabilitation for people with TIA and mild stroke, and no studies appear to have investigated the cost-effectiveness or implementation determinants of such programs. If successful, the CVR program will improve health outcomes and quality of life of people who have had a TIA or mild stroke, guiding future research, policy, and clinical practice, reducing the risk of repeat heart attacks and strokes for this population.

**Trial registration:**

Australian New Zealand Clinical Trials Registry (ANZCTR): ACTRN12621001586808, Registered 19 November 2021.

**Supplementary Information:**

The online version contains supplementary material available at 10.1186/s12913-022-08797-3.

## Background

In Australia and globally, cardiovascular disease (CVD) is the leading cause of death [1, 2]. CVD includes disorders of the heart and blood vessels such as coronary heart disease, ischaemic stroke and transient ischaemic attack (TIA) [3]. One in three CVD events are repeat events and these are more likely to be fatal and result in a higher burden of disease cost than initial events [4–6]. Recurrent stroke occurs in 11% of stroke survivors within one year, and 39% of stroke survivors within 10 years [7]. In addition, during the first 90 days following a TIA, individuals have a 15–20% risk of suffering a stroke [8]. Cardiac disease and recurrent stroke are the leading causes of mortality after stroke [9, 10]. In 2020, there were 445,000 stroke survivors living in Australia, and this is predicted to increase to an estimated 820,000 in 2050 [11]. The current international recommendation is that every person with CVD should be referred to a secondary prevention program, such as cardiac rehabilitation, to prevent recurrent CVD events, such as stroke and heart attacks [12–14]. However, evidence suggests that minimal secondary prevention services are provided post-stroke and TIA [15, 16].

There is strong evidence for exercise-based cardiac rehabilitation in people with heart disease, which can be defined as a comprehensive secondary prevention program which addresses modifiable risk factors for CVD using exercise and education [17]. Ischaemic stroke, TIA and coronary heart disease share many modifiable risk factors such as hypertension, smoking, physical inactivity, poor diet, obesity and excessive alcohol consumption [18]. Cardiac rehabilitation improves risk profiles, decreases hospital admissions and mortality, increases medication adherence and improves quality of life in those with heart disease [17]. It has been reported that a high proportion of stroke survivors have poor knowledge of stroke risk factors [19, 20] and control of cardiovascular health is suboptimal post stroke [21, 22]. Thus, cardiac rehabilitation may be a suitable option for secondary prevention for people with TIA and stroke [23, 24].

Previous research has found that despite the proposed suitability of cardiac rehabilitation, people with stroke or TIA are not routinely attending cardiac rehabilitation programs around the world [25, 26]. In Australia, a national survey of cardiac rehabilitation coordinators, conducted in 2018, found that less than 2% of the cardiac rehabilitation population were people with a diagnosis of stroke/TIA, and less than 6% of cardiac rehabilitation coordinators received referrals for this group of patients in the previous year [25]. However, over half of the cardiac rehabilitation coordinators thought that cardiac rehabilitation was appropriate for people with a primary diagnosis of TIA (60%) or mild stroke (54%). Transient symptoms, minimal disability from a mild stroke and similar risk factors for stroke and cardiac disease were common reasons reported for why mild stroke or TIA patients should be included in cardiac rehabilitation. Recently, the views of stroke health professionals in Australia were explored, finding that only 30% of stroke health professionals referred people with TIA and mild stroke to secondary prevention programs, despite over 90% of stroke health professionals believing cardiac rehabilitation to be an appropriate form of secondary prevention [27]. The top three barriers to cardiac rehabilitation for this population as perceived by the stroke health professionals were the name of the program, lack of referrals and lack of funding [27]. Both cardiac rehabilitation and stroke health professionals agreed that the similar exercise, education and supervision needs of people with cardiac disease and TIA or mild stroke were key enablers for cardiac rehabilitation inclusion [27]. Similar results have been found in surveys of cardiac rehabilitation and stroke health professionals in Canada, Switzerland and Ireland [23, 26, 28, 29].

The evidence for people with TIA or stroke attending cardiac rehabilitation is limited. One large randomised controlled trial has recently been reported, the PREVENT trial, finding modest effects on vascular risk factors for stroke following a 12-week exercise and education program for people with TIA or mild stroke [30]. Two small randomised controlled trials have also been identified in the literature, although it is unclear whether these studies are stroke only cardiac rehabilitation programs or integrated programs (TIA, stroke, heart disease) [31, 32]. Additionally, the inclusion criteria differ between studies. One study included participants > 1 year post stroke and any severity [31], while the other studies included people with TIA and mild stroke within one month [32] and three months [30] of diagnosis. There is some evidence of integrated cardiac rehabilitation programs, including participants with TIA, mild stroke and coronary heart disease, using pre-post study designs [33–35]. Despite this limited evidence, all studies found that the cardiac rehabilitation model was feasible in this population, improving fitness and reducing cardiovascular disease risk [30–35]. Utilising existing cardiac rehabilitation programs for people with TIA or mild stroke may positively impact health status without creating new programs, but more robust evidence is required to determine its impact on physical function, risk factors, quality of life, morbidity and mortality, including the feasibility of conducting integrated cardiac rehabilitation programs within health services and its cost-effectiveness [26]. With no consensus on comprehensive secondary prevention programs for people post-TIA or stroke at present, and existing cardiac rehabilitation programs being a potentially suitable option, our research questions are:Is an integrated (TIA, mild stroke, heart disease) traditional exercise-based cardiac rehabilitation program effective in improving functional exercise capacity (6-min walk test distance) and quality of life, and reducing the risk of unplanned CVD-related hospital admissions, for people with TIA or mild stroke during the 6-months following commencement of the traditional cardiac rehabilitation program compared to usual care?Can an integrated traditional exercise-based cardiac rehabilitation program be implemented in existing health services, considering implementation outcome measures such as acceptability, feasibility, adoption, fidelity, and cost?

## Methods

### Design

The type 1 effectiveness-implementation hybrid study [36] will use a 2-arm single-centre assessor-blind randomised controlled trial design and will be conducted in Canberra, Australia, commencing in 2022 (Fig. 1). People with TIA and mild stroke will be randomised to a 6-week exercise-based Cardiovascular Rehabilitation (CVR) program or a usual care 6-month wait-list control group. Recruitment will be staggered over 18-months and the total study duration for each participant will be 6-months from commencing the study.

**Fig. 1 Fig1:**
[figure not shown]
Flow of participants through the CRAMS trial**.** CVR, cardiovascular rehabilitation; TIA, transient ischaemic attack

### Randomisation

An investigator not involved in recruitment or assessments will use a computer-generated random number sequence, with participants allocated in a 1:1 ratio. Group allocation will be concealed using sealed, consecutively numbered opaque envelopes. Following each participant’s baseline assessment, the next envelope in the sequence will be opened to reveal random allocation to one of two groups: the Cardiovascular Rehabilitation program or the 6-month wait-list control group.

### Participants

Participants will be recruited by health professionals from two hospitals (Canberra Health Services and Calvary Public Hospital Bruce) in-person or via mail using an existing TIA and stroke database, and from primary healthcare services within the Australian Capital Territory, Australia. All potential participants that express interest in participating in the study will be assessed by healthcare professionals and the research team to determine their eligibility. A research assistant will obtain written informed consent from all eligible participants on entry to the study (Supplementary File 1).

To be eligible, participants must be 18 + years old; have a medically documented TIA or mild non-disabling ischaemic stroke (National Institutes of Health Stroke Scale (NIHSS) score 0–4 [37]; modified Rankin Scale score ≤ 2 [38]) within the previous 12 months on discharge from the emergency department or the hospital ward, where applicable; and reside in the Australian Capital Territory, Australia. Participants will be excluded if they have an uncertain diagnosis; evidence of intracranial haemorrhage on a CT or MRI study; undergone recent (< 30 days) carotid endarterectomy; have evidence of a disabling stroke as measured by modified Rankin Scale score of ≥ 3; New York Heart Association class II-IV symptoms of heart failure; uncontrolled arrhythmias; severe chronic obstructive pulmonary disease; uncontrolled hypertension; symptomatic peripheral artery disease; unstable angina; uncontrolled diabetes; inadequate English language skills, including significant speech impairment, or cognitive skills; unable to perform a submaximal walking test or wear an accelerometer due to disability (e.g., confined to a wheelchair) or they have previously completed cardiac rehabilitation within the last 5 years.

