### Cardiovascular Rehabilitation (CVR) program

The CVR program included in this study is typical of most contemporary phase II cardiac rehabilitation programs in Australia [14, 39]. The CVR program is multidisciplinary, time-limited (once a week, 6-weeks), conducted in groups, health service-based, and has educational and supervised exercise components (one hour education plus one hour exercise per week). Members of the multidisciplinary team include exercise physiologists, physiotherapists, dietitians, psychologists, pharmacists and supervised university health students. The intention of the CVR program is not to replace other treatment services that may be required after a mild stroke to address any deficits such as speech or motor impairments but rather provide a comprehensive program for CVD risk factor modification and management.

The main aim of the exercise sessions will be to increase exercise capacity by exercising large muscle groups at a moderate intensity [14]. The best predictor of an increased risk of death from any cause in men with cardiovascular disease is exercise capacity [40]. For every 1-MET increase in exercise, there is a 9% improvement in survival [40]. The exercise sessions will be conducted in the same way as a typical cardiac rehabilitation program as many cardiac rehabilitation participants have co-morbidities, including stroke [41]. All exercise sessions will be individually tailored for each of the participants, including aerobic and resistance training, and supervised by a physiotherapist and/or exercise physiologist.

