Members of the multi-disciplinary team will conduct education sessions to increase the participant’s knowledge of their CVD condition and increase self-management skills for risk factor management. The education will be slightly modified compared to a typical cardiac rehabilitation program to include the anatomy and physiology of the brain, TIA and ischaemic stroke, and the management of stroke risk factors. The education sessions will cover: cardiac and brain anatomy and physiology; cardiac and stroke risk factors, modification and management of symptoms; how to deal with stress, anxiety and depression; cardiac and stroke medications; benefits of exercise and physical activity; and nutrition advice. People with heart disease will be recruited to this program to replicate a standard phase II cardiac rehabilitation program currently offered in Australia and to enable the integration of people with TIA, mild stroke, and heart disease in the same program. However, research outcomes will not be collected or analysed for this group as the evidence base for exercise-based cardiac rehabilitation for people with heart disease is well established [17].

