### Usual care control group

Those randomised to the control group will participate in usual care following a TIA or mild stroke. In Australia, this typically consists of follow-up with a neurologist and little or no secondary prevention other than pharmacological management [42]. Control participants will be wait-listed for the CVR program and will commence the CVR program 6-months after they have completed their baseline measures.

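### The prior-rehabilitation exclusion covers only completed programmes, so someone now attending or booked into equivalent cardiac rehabilitation can be randomised to control

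*Protocol article*

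**What the plan says.** All references are to the protocol article.

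- **Participants.** The exclusion for earlier rehabilitation applies if "they have previously completed cardiac rehabilitation within the last 5 years". The cardiac exclusions are "New York Heart Association class II-IV symptoms of heart failure; uncontrolled arrhythmias" and, further along the same list, "symptomatic peripheral artery disease; unstable angina; uncontrolled diabetes". Stable coronary disease, or a past cardiac event without these features, is not listed.
- **Cardiovascular Rehabilitation (CVR) program.** The intervention is presented as ordinary cardiac rehabilitation: "The CVR program included in this study is typical of most contemporary phase II cardiac rehabilitation programs in Australia". The section adds that "many cardiac rehabilitation participants have co-morbidities, including stroke", and that "People with heart disease will be recruited to this program to replicate a standard phase II cardiac rehabilitation program currently offered in Australia".
- **Background.** It cites an international recommendation that "every person with CVD should be referred to a secondary prevention program, such as cardiac rehabilitation".
- **Usual care control group.** Usual care is described as neurologist follow-up with hardly any secondary prevention beyond drugs. On access to the trial programme: "Control participants will be wait-listed for the CVR program and will commence the CVR program 6-months after they have completed their baseline measures". Nothing is said about cardiac rehabilitation reached through a cardiac diagnosis.
- **Sample size.** 128 evaluable participants (64 per arm), raised to 140 for 8% dropout, with no allowance for controls who receive rehabilitation.

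**The concern.** The evident purpose of the criterion is to keep out people already exposed to the intervention. As worded, it removes someone who finished a programme almost five years ago but admits someone who is part-way through one today or has a start date next week. For the randomised comparison the second person is the greater problem: if allocated to control, they receive something very close to the tested programme between baseline and 6 months.

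Under the planned analysis by assigned group, each such control narrows the difference in 6-minute walk distance. The bias runs towards no difference, in a trial sized with almost no power to spare. The article also names no item that would show by arm how many participants had rehabilitation outside the trial.

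**Working it through.** **1. Is the route open on the text?**

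| Person with TIA or mild stroke and stable heart disease | Caught by the exclusion? |
|---|---|
| Completed cardiac rehabilitation within 5 years | Yes |
| Attending it now, not yet finished | No |
| Booked to start it | No |

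The second and third can be randomised to control. The wait-list rule governs the CVR programme of the trial, not a cardiac rehabilitation place held elsewhere. Since the CVR programme is described as typical of Australian phase II programmes, that place is close to the intervention itself.

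**2. Reproduce the plan's sample size.** Inputs from the Sample size section: Hedges' g = 0.41, f = 0.205, m = 3 measures, correlation ρ = 0.5, two-sided α = 0.05, power 80%. For the between-groups effect in a repeated-measures ANOVA:

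λ = f² × N × m / [1 + (m − 1)ρ], with 1 and N − 2 degrees of freedom.

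- N = 128: λ = 0.205² × 128 × 3 / 2 = 0.042025 × 192 = 8.07, power 0.805.
- N = 126: power 0.799, just below target.
- Dropout: 128 / 0.92 = 139.1, giving 140 for equal arms.

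Both 128 and 140 reproduce. The within-between interaction form would give 40, and a single two-mean comparison 188, so the between-groups form is the one used.

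**3. Add dilution.** Let c be the share of controls who receive equivalent rehabilitation. The document gives no value, so c is an assumption. If each such control gains the full programme effect and the standard deviation is unchanged, the contrast becomes 0.41 × (1 − c) and f becomes 0.205 × (1 − c).

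| c (assumed) | Controls affected, of 64 | Effect size | λ at N = 128 | Power at N = 128 | N for 80% power | Randomised (N / 0.92, rounded up) |
|---|---|---|---|---|---|---|
| 0% | 0 | 0.410 | 8.07 | 0.805 | 128 | 140 |
| 2% | 1.3 | 0.402 | 7.75 | 0.789 | 132 | 144 |
| 5% | 3.2 | 0.389 | 7.28 | 0.764 | 140 | 153 |
| 10% | 6.4 | 0.369 | 6.54 | 0.718 | 156 | 170 |

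A control who gains less than the full effect dilutes less, so each row is the pessimistic case for its share.

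**The case against.** Several points on the other side are sound and limit the finding.

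- **The wait-list.** A reader might infer that controls can slip into the trial's own classes through the places for people with heart disease. The text does not support this: controls start the CVR programme only after 6 months, and earlier entry would breach that rule.
- **Data collection.** A reader might infer that nothing collected could reveal outside rehabilitation, so that a null result could never be told apart from dilution. That goes too far. The Costs section covers non-trial healthcare use with an open-ended example, which could pick up some of it, and a journal article need not list every survey item. What stands is that no such item is named for reporting by arm.
- **Frequency.** The remark about co-morbidities describes people in cardiac rehabilitation. It gives no rate of heart disease, or of cardiac referral, among people with TIA or mild stroke. The Background figure of less than 2% is the stroke/TIA share of the cardiac rehabilitation population. Its denominator is the wrong one, so it neither supplies the rate nor shows it to be negligible.
- **Training before baseline.** Rehabilitation received earlier is balanced in expectation by randomisation, and walk distance is measured at baseline. It does not bias the comparison in the way that exposure of controls during follow-up does.
- **New cardiac events.** Rehabilitation that follows a cardiac event during follow-up is arguably part of usual care, and no entry criterion can prevent it.

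None of this closes the gap for people who, at entry, are already attending or hold a place in an equivalent programme outside the trial.

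**Conclusion.** The point holds in a limited form. The exclusion is a stated rule that selects on the wrong feature, completion, and leaves in the people whose exposure would fall inside the comparison period. The consequence is dilution towards no difference, not a false positive.

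Its size cannot be derived from the document. If 2% to 10% of controls were affected and each gained the full effect, power would fall from 0.805 to between 0.789 and 0.718. At the low end that is about one person in the control arm and 1.6 percentage points of power, so the practical effect may be small. The arithmetic should not be read as showing that 128 or 140 is wrong: both reproduce from the stated inputs. This is a cheap improvement.

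**What to change.** 1. In Participants, reword the last exclusion to: *completed cardiac rehabilitation within the last 5 years, or currently attending it or booked to start it*. It need not reach anyone who merely began a programme within 5 years or has only been referred. That would shed more recruits, and narrow a trial of an integrated programme, for a debatable gain.
2. Add one item to the survey already given at 6 weeks and 6 months, in both arms: attendance at cardiac or other supervised exercise rehabilitation outside the trial (yes/no, number of sessions). Report it by arm.
3. State that rehabilitation after a new cardiac event during follow-up remains part of usual care and is only recorded.

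**Cost:** a one-line eligibility amendment, one survey question, and the loss of a few otherwise eligible people. The number lost cannot be estimated from the document, and the Discussion already lists low recruitment as a possible limitation. That is the reason to keep the added exclusion to current or booked attendance.
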